Tranexamic acid inhibits the fibrinolytic response by inhibiting the conversion of plasminogen to plasmin. Normally, plasmin breaks down fibrin to fibrin degradation products thereby weakening the clot. By lowering the concentration of plasmin by the administration of tranexamic acid, the breakdown of the cloth will be inhibited. There is some body of evidence suggesting the beneficial effect of tranexamic acid on the perioperative blood loss and transfusion [13–15]. A small blinded randomized prospective study found a reduction of 36% in blood loss in 27 tangential burn excisions by administrating 20 mg/kg tranexamic acid intravenous [13], while a small RCT with 50 patients performed in India showed a reduction of 41% of perioperative blood loss with 15 mg/kg tranexamic acid intravenous [14]. Furthermore, a retrospective study reported a 30% decrease in transfusions during burn excisional surgery by administration of 10 mg/kg tranexamic acid intravenous followed by a continuous infusion of 1 mg/kg/h [15]. However, no study investigated the fibrinolytic state of burn patients during burn excisional surgery. There is sufficient evidence available for the safety of the use of tranexamic acid in other patient categories. Several large studies, CRASH-II and III trial [16, 17], WOMAN-trial [18], and a recent retrospective case–control study [19], have investigated possible thromboembolic complications of the use of tranexamic acid in trauma patients, during orthopedic surgery and women with postpartum hemorrhage, and reported no higher incidence in any complication in the tranexamic acid group.

The perioperative monitoring of coagulation and especially fibrinolysis using classic hemostatic tests is difficult [3]. More real-time test like thrombelastography (TEG) or rotational thromboelastometry (ROTEM) could give insight especially in the state of the fibrinolytic system [1, 10]. Schaden et al. reported a reduction in transfusion during burn excisional surgery by using a coagulation management protocol including ROTEM [9, 20]. While ROTEM is promising, ROTEM could miss moderate fibrinolysis [12]. To further study the fibrinolytic system, more in-depth laboratory tests are needed. For example, plasmin-α2-antiplasmin complex is a separate test and is a more sensitive parameter to investigate the occurrence of fibrinolysis.

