### Objectives {7}

#### Research hypothesis

Tranexamic acid reduces the volume of blood loss during burn excisional surgery, irrespectively of the presence of hyper fibrinolysisDuring burn surgery, a significant effect of hyper fibrinolysis is present due to the stress of burn trauma

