### Intervention description {11a}

Patients will be prepared for surgery and anesthetized following the current standard of care. Both the placebo as the tranexamic acid will consist of an infusion bag of a total volume of 100 ml and will be indistinguishable for study personnel. See Fig. 1 for the complete timeline of study procedures. During induction of anesthesia, but before incision, the study medication will be administered over a period of 15 min, not surpassing the maximum delivery rate of tranexamic acid of 100 mg/minute. The intervention group will receive 1500 mg tranexamic acid intravenous. The placebo group will receive a sodium chloride 0.9% bolus.

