### Outcomes {12}

Primary outcome:The volume of blood loss in milliliter/% BSA excised measured during surgery

Secondary outcome:The occurrence and magnitude of fibrinolysis/coagulopathy during burn excisional measured by, among others, ROTEM-analysis, the measurement of global fibrinolysis and D-dimerGraft take of the split skin graft on the area of excision measured in the percentage of vital graft 5 days surgeryHospital mortalityLength of (ICU) stayCardiopulmonary (i.e., arterial embolism)/ neurologic complication (i.e., stroke) (at 3 months after the study procedure)Need for escape medication (tranexamic acid 1000 mg) in case of uncontrolled bleedingThe need for red blood cell transfusion peri-procedural

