## Assignment of interventions: allocation

### Sequence generation {16a}

Participants will be randomized into two groups (1:1 allocation ratio) using the randomization tool in Castor EDC (Castor EDC, Ciwit BV, Amsterdam, The Netherlands). Variable block randomization will be used, stratified by study site. The block size will be set to 2, 4, and 6 as the possible minimum number of inclusions per center is 16. The study team is always concealed of the sequence of randomization, current randomization or previous randomizations.

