## Statistical methods

### Statistical methods for primary and secondary outcomes {20a}

Blood loss will be tested for normal distribution; if normally distributed, the mean with standard deviation will be reported, and differences between the two groups will be tested using Student’s *T*-test. Otherwise, a median with a 25–75% confidence interval will be reported and differences will be tested using a Mann-Whitney *U* test. For secondary outcome parameters, continuous variables (i.e., volume of blood loss, extent of hyperfibrinolysis) will be tested for normal distribution. If they are normally distributed, the mean with standard deviation will be reported and differences will be tested using Student’s *T*-test. Otherwise, a median with a 25–75% confidence interval will be reported, and differences will be tested using a Mann-Whitney *U* test. Binomial data will be reported using percentages, and differences will be tested using chi-squared tests.

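### The tests stated for fibrinolysis compare the arms and so measure the drug's effect, while the objective and second hypothesis ask whether fibrinolysis occurs during burn surgery in patients not given the drug

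*Protocol article*

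**What the plan says.** All references are to the protocol article.

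- **Objectives {7}.** The fibrinolysis question stands under Primary objective, next to the blood-loss question, and is not worded as an arm contrast. The second research hypothesis is that "a significant effect of hyper fibrinolysis is present due to the stress of burn trauma".
- **Background and rationale {6a}.** No earlier study is said to have examined the fibrinolytic state of burn patients during this surgery. On mechanism: "Tranexamic acid inhibits the fibrinolytic response by inhibiting the conversion of plasminogen to plasmin".
- **Outcomes {12}.** Listed as secondary: "The occurrence and magnitude of fibrinolysis/coagulopathy during burn excisional measured by, among others, ROTEM-analysis". No arm is specified.
- **Sequence generation {16a} and Intervention description {11a}.** "Participants will be randomized into two groups (1:1 allocation ratio"; and "During induction of anesthesia, but before incision, the study medication will be administered over a period of 15 min". ROTEM is planned before surgery and during it, 1 h after incision.
- **Statistical methods {20a}.** For secondary outcomes "continuous variables (i.e., volume of blood loss, extent of hyperfibrinolysis) will be tested for normal distribution"; if normal, "the mean with standard deviation will be reported and differences will be tested using Student’s *T*-test", otherwise a median and a Mann-Whitney test. "Binomial data will be reported using percentages, and differences will be tested using chi-squared tests".
- **Additional analyses {20b}.** Marked not applicable, with no subgroup analysis planned.
- **Rescue medication.** Open tranexamic acid can be given in either arm for massive uncontrollable bleeding.

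**The concern.** The objective and the second hypothesis concern the surgical burn patient as found, without the drug. By the article's own account of mechanism, the active arm no longer shows that state once the infusion has been given, and every intraoperative sample in that arm comes after it. The placebo arm and the pre-dose samples still carry the information.

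The tests named for fibrinolysis do not use that information in the way the question needs. A comparison of independent groups asks whether the drug changes fibrinolysis. It neither estimates how often fibrinolysis occurs nor tests whether it rises from the pre-surgery sample. One of the trial's two stated main goals, and the gap in knowledge that the introduction identifies, therefore lacks a matching analysis in a plan that does name tests for this outcome. An analysis plan that followed this section faithfully would inherit the mismatch.

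**Working it through.** **1. The plan's own figure.** The only sample-size figure is for blood loss. Inputs from Sample size {14}: mean 194, SD 81 ml/% BSA, 25% reduction, type I error 5% (taken as two-sided), power 80%.

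- Difference = 0.25 × 194 = 48.5.
- The two-sample t-test calculation gives 44.8, so 45 per arm (power 0.802) and 90 in total.
- 90 / 0.95 = 94.7, so 95.

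The figure reproduces. It does not bear on the fibrinolysis objective, for which no figure is stated, but it gives the base: about 45 evaluable placebo patients.

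**2. Question against test.**

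| Question in the article | Quantity needed | What the stated tests give |
|---|---|---|
| Does fibrinolysis occur during surgery? | Proportion in patients without the drug, with its uncertainty | Difference in proportions between arms |
| To what extent? | Level in patients without the drug, or change from their pre-surgery value | Difference in level between arms |
| Is hyperfibrinolysis present? | Comparison with a threshold or with the patient's own earlier sample | No such comparison |

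The section says that the comparison is between the two groups for blood loss. It does not repeat this for secondary outcomes, but the same tests are named and arms are the only groups defined. None of the named tests is a paired test.

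**3. Why an arm difference does not determine occurrence.** Let p be occurrence without the drug and s the fraction that the drug suppresses. Expected arm difference = p − p(1 − s) = p × s. All values of p and s below are assumptions.

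| p | s | Difference p × s | Approximate power, 45 per arm |
|---|---|---|---|
| 30% | 0 | 0 points | – |
| 30% | 50% | 15 points | 40% |
| 50% | 50% | 25 points | 69% |
| 50% | 90% | 45 points | above 99% |

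With s = 0 the difference is zero whatever p is. A 15-point difference fits p = 30% with s = 50%, and equally p = 50% with s = 30% (0.50 × 0.30 = 0.15). The difference alone cannot recover p. A non-significant test would also be likely (60%) in the second row, where fibrinolysis occurs in nearly a third of untreated patients.

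**4. Precision of a placebo-arm estimate.** Wilson 95% intervals, with z = 1.96 and observed proportion x/n: centre = (x/n + z²/2n) / (1 + z²/n), half-width = z × √[(x/n)(1 − x/n)/n + z²/4n²] / (1 + z²/n).

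- 22/45 (about 50%): centre 0.490, half-width 0.140, so 35% to 63%.
- 14/45 (about 30%): 20% to 46%.
- If only 15 placebo patients had the single-center assays (an assumption; the article gives no number), 8/15 gives 30% to 75%.

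**The case against.** The strongest reply is that the same section also promises means with SD, medians or percentages. In a two-arm trial these would naturally be given by arm, and the placebo column would then describe fibrinolysis in patients not randomised to the drug. This stands in part: the planned data can answer the objective. But a placebo summary of that kind is not a paired comparison with the pre-surgery sample, tests no hypothesis about presence, and is not named as the answer to the objective.

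A second reply is that fibrinolysis is listed as secondary under Outcomes and that the trial is powered only on blood loss. That is true and limits the weight of the point, but the Objectives section still places the question under the primary objective.

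A third is that such detail belongs in an analysis plan that is not shown. A threshold for hyperfibrinolysis or a rule for samples after rescue may well be there, and their absence here is not held against the article. The point is that the article fixes tests for this outcome that do not fit its objective.

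Two stronger readings are not supported. A reader might infer that the arms will be pooled, so that occurrence is understated (with p = 30% and s = 50%, (30 + 15)/2 = 22.5%). No section plans pooling. A reader might also take the introduction's figure of more than 50% as the expected occurrence. It refers to disturbance of the fibrinolytic system in trauma patients, not to fibrinolysis in burn surgery. Nor does the article say how completely the drug suppresses fibrinolysis.

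**Conclusion.** The point holds as a mismatch between a stated objective and its stated tests. The tests named for fibrinolysis estimate a drug effect. They do not test whether fibrinolysis occurs during burn surgery or changes from the pre-surgery sample, and they cannot test the second hypothesis. It would go too far to say that the trial cannot answer the question: the samples are planned, and by-arm summaries would give part of the answer.

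The size of the problem cannot be stated as a bias, because no biased estimate is planned. What can be stated is the base on which a proper answer rests: about 45 placebo patients for ROTEM, with a 95% interval of roughly ±14 points if occurrence were about 50%. The base is smaller for D-dimer and global fibrinolysis, which appear to be taken only in the coordinating center.

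This rests on reading the secondary-outcome tests as between arms and on 45 evaluable patients per arm. The number of placebo patients who receive rescue tranexamic acid is unknown. The blood-loss analysis is unaffected.

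**What to change.** In Outcomes {12} and Statistical methods {20a}, state that the objective on occurrence and extent of fibrinolysis is answered in the placebo arm by:

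- the within-patient change in ROTEM lysis from the pre-surgery to the intraoperative sample, with a paired analysis;
- the proportion with hyperfibrinolysis, by a threshold set in advance, with its 95% CI;
- only samples taken before any rescue tranexamic acid, with the number excluded reported;
- the same analyses of D-dimer and global fibrinolysis in the center that collects them, with the smaller number stated.

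Keep the between-arm comparison as a separate outcome, labelled as the drug's effect on fibrinolysis, and say that the arms will not be pooled to estimate occurrence.

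**Cost.** Wording only; all samples are already planned. The stated base for this objective falls from the whole trial to about 45 patients for ROTEM. Three limits should be written down. Leaving out samples after rescue may remove some of the heaviest bleeders, and it needs the time of rescue to be known relative to the sample. A paired change shows that fibrinolysis is present and moves during surgery, but does not by itself attribute it to the burn. And the article itself notes that ROTEM could miss moderate fibrinolysis, so a ROTEM-based proportion may be too low.

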$$\begin{array}{c}\mathrm{Total}\;\mathrm{blood}\;\mathrm{loss}\;(\mathrm{ml})\;=\;\mathrm{total}\;\mathrm{red}\;\mathrm{cell}\;\mathrm{loss}\;(\mathrm{ml})\;/\;(\mathrm{hematocrit}\;\mathrm{before}\;\mathrm{surgery}\;-\;\mathrm{hematocrit}\;\mathrm{after}\;\mathrm{surgery})\\\mathrm{Total}\;\mathrm{red}\;\mathrm{cell}\;\mathrm{loss}\;(\mathrm{ml})\;=\;\mathrm{accepted}\;\mathrm{red}\;\mathrm{cell}\;\mathrm{loss}\;(\mathrm{ml})\;+\;\mathrm{volume}\;\mathrm{of}\;\mathrm{transfused}\;\mathrm{red}\;\mathrm{blood}\;\mathrm{cells}\\\mathrm{Accepted}\;\mathrm{red}\;\mathrm{cell}\;\mathrm{loss}\;=\;\mathrm{Estimated}\;\mathrm{volume}\;\ast\;(\mathrm{hematocrit}\;\mathrm{before}\;\mathrm{surgery}\;-\;\mathrm{hematocrit}\;\mathrm{after}\;\mathrm{surgery})\\\mathrm{Estimated}\;\mathrm{volume}\;\mathrm{in}\;\mathrm{men}\;=\;\mathrm{weight}\;(\mathrm{kg})\;\ast\;70\;\mathrm{in}\;\mathrm{women}\;\mathrm{weight}\;(\mathrm{kg})\;\ast\;65\;(\mathrm{formula}\;\mathrm{of}\;\mathrm{Moore})\end{array}$$

Blood sample will be taken at three time points during the intervention: before surgery, 1 h after incision, and 6 h after finishing surgery. The blood samples consist of the following analysis: before surgery: hemoglobin, electrolytes (sodium/potassium), kidney function (urea/creatinine), albumin, ROTEM, basic coagulation test (INR/APTT/thrombocytes/fibrinogen); during surgery: ROTEM; after surgery: hemoglobin and hematocrit. In addition to the above-described analysis, additional blood samples will be taken in all patients studied in the Maasstad Hospital. When surgery is ≥ 1.5 h, an additional ROTEM will be determined at the end of surgery. Furthermore, in the Maasstad Hospital, additional samples will be collected to investigate the burn coagulopathy during the perioperative period (i.e., global fibrinolysis, D-dimer, anti-thrombin III, etc.).

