### Participant timeline {13}

When a potential participant is scheduled for burn excisional surgery, the patient is informed about the study and informed consent is taken. See Fig. 1 for the complete timeline for the participant. Informed consent is usually taken in the 2-3 days before surgery. After consent, the patients are randomized. A blood sample is taken before surgery to establish a baseline. During surgery, two more blood sample will be taken, and one blood sample will be taken 6–12 h after surgery. Hereafter, the study procedure is finished for the patient. After 3 months, the patient will be contacted to inform whether cardiopulmonary of neurologic complications have occurred.

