### Sample size {14}

In a small retrospective group of 109 patients (unpublished) with ≥ 250 ml blood loss from Burn Centre Rotterdam, we found a mean blood loss of 1.01 ± 0.56 ml/cm^2^ or 194 ± 81 ml/% BSA excised. In a small blinded RCT study, Jennes et al. found a reduction of 36% in blood loss in 27 tangential burn wound excisions when administering tranexamic acid [12]. A small RCT with 50 patients performed in India showed a reduction of 41% blood loss in burn patients when using tranexamic acid [13]. Orthopedic literature shows a somewhat more limited blood loss reduction of approximately 25% with the use of 1–2 g of tranexamic acid during surgery [20, 22, 23]. Therefore, based on a mean blood loss of 194 ml/% BSA excised with an SD of 81 ml, demonstrating a 25% reduction in blood loss with type I and type II error rate of 5% and 20% respectively, we require 45 patients per arm, for a total of 90 patients. Taking a dropout rate of 5% into account, we aim to include 95 patients in our study.

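### The between-arm test for extent of fibrinolysis makes no stated use of the pre-surgery value, although ROTEM is run before and during surgery at all sites; the test is valid but less precise than it could be

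*Protocol article*

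**What the plan says.** Section {20a} of the protocol article states that, for secondary outcomes, "continuous variables (i.e., volume of blood loss, extent of hyperfibrinolysis) will be tested for normal distribution". Normally distributed variables are compared by Student's t-test, others by the Mann-Whitney test, and binomial data by chi-squared tests. No covariate, change score or other use of a baseline is named, and section {20b} marks additional analyses as not applicable.

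The data collection does provide a baseline. Participant timeline {13}: "A blood sample is taken before surgery to establish a baseline". The text after the blood-loss formula in Intervention description {11a} lists the assays. Before surgery these include "albumin, ROTEM, basic coagulation test (INR/APTT/thrombocytes/fibrinogen); during surgery: ROTEM; after surgery: hemoglobin and hematocrit". The intra-operative sample is timed at 1 h after incision. The further assays come from one centre: "in the Maasstad Hospital, additional samples will be collected to investigate the burn coagulopathy during the perioperative period (i.e., global fibrinolysis, D-dimer".

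Outcomes {12} places occurrence and magnitude of fibrinolysis among the secondary outcomes and names ROTEM, global fibrinolysis and D-dimer as its measures.

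**The concern.** The study drug is infused during induction of anaesthesia, so a sample drawn before surgery as a baseline is read here as a pre-dose value. The same assay is repeated after dosing. Where the two values are correlated, part of the spread in the later value is already explained by the earlier one. A two-sample test leaves that part in the error term.

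The protocol itself expects patients to differ before dosing. Its background describes considerable change in coagulation status after severe burns, and the inclusion criteria show that time since the burn varies. Randomisation is stratified by centre only, so nothing in the design balances baseline coagulation.

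At stake is the precision of the estimated drug effect on fibrinolysis, an outcome for which no sample size was calculated. A wider interval than necessary makes a real effect easier to miss.

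**Working it through.** **1. Which measures have a value before and during surgery, according to the text**

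| Measure | Sites | Before surgery | During surgery |
|---|---|---|---|
| ROTEM | all | yes | yes |
| INR, APTT, thrombocytes, fibrinogen | all | yes | not listed |
| Global fibrinolysis, D-dimer, antithrombin III | Maasstad only | perioperative, times not itemised in the text | perioperative, times not itemised in the text |

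The all-site case therefore rests on ROTEM. The Maasstad assays qualify where paired samples exist.

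**2. The plan's own power figure**

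The inputs in Sample size {14} are a control mean of 194 and an SD of 81 (both in ml per % BSA), a target reduction of 25%, a 5% significance level and 80% power. Its conclusion is "we require 45 patients per arm, for a total of 90 patients".

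- Difference: 0.25 × 194 = 48.5. Standardised: 48.5 / 81 = 0.599.
- Normal approximation: n = 2 × (1.960 + 0.842)² × 81² / 48.5² = 43.8, so 44 per arm.
- t-test solution: 44.8, so 45 per arm. Power at 45 per arm is 80.2%.
- With 5% dropout: 90 / 0.95 = 94.7, so 95.
- A one-sided test would need only 35 per arm, so the plan's figure is two-sided.

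The stated figure reproduces, but it concerns blood loss, which has no pre-dose value. No corresponding input is given for fibrinolysis.

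**3. Effect of baseline adjustment**

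With correlation r between the pre-surgery and intra-operative values, the ANCOVA residual SD is SD × √(1 − r²). Ignoring the one degree of freedom used by the covariate:

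adjusted power = Φ[(1.960 + z_power) / √(1 − r²) − 1.960]

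Example, assumed unadjusted power 80% and r = 0.5: (1.960 + 0.842) / 0.866 − 1.960 = 1.275, and Φ(1.275) = 89.9%.

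| Assumed r | Power after adjustment, from 80% | Gain (points) |
|---|---|---|
| 0 | 80.0% | 0 |
| 0.2 | 81.6% | 1.6 |
| 0.3 | 83.6% | 3.6 |
| 0.4 | 86.4% | 6.4 |
| 0.5 | 89.9% | 9.9 |
| 0.6 | 93.8% | 13.8 |
| 0.7 | 97.5% | 17.5 |

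The starting power is also an assumption. At r = 0.5, starting from 50%, 60%, 70% and 90%, the gains are 11.9, 12.4, 11.8 and 6.3 points.

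In patient numbers, the requirement scales with 1 − r². At r = 0.5, 45 × 0.75 = 33.75, so about 34 per arm would give the precision of 45 unadjusted.

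**4. If the analysed variable is a change from baseline**

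Section {20a} does not say whether extent is the later value or a change. With equal variances before and during surgery, a change score has variance 2(1 − r)σ², against (1 − r²)σ² for ANCOVA. The ratio of ANCOVA to change score is (1 + r)/2, which never exceeds 1. At r = 0.5 the change score has variance 1.00σ², no better than the later value alone, while ANCOVA has 0.75σ². At r = 0.2 the figures are 1.60σ² and 0.96σ².

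**The case against.** The strongest reply is that nothing stated is wrong. Under randomisation the unadjusted comparison is unbiased, and its 5% error rate already allows for chance baseline imbalance. A reader might infer that a baseline difference could be mistaken for a drug effect beyond the nominal error rate; the document does not support that. This part of the objection stands, and the point is one of precision only.

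Several limits on scope also stand:

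- A reader might infer that every fibrinolysis measure has a baseline in every patient. Two of the three named measures, global fibrinolysis and D-dimer, come from the Maasstad Hospital only.
- A reader might infer that the baseline is discarded. As {20a} leaves the analysed variable open, a change score would be compatible with the text. Step 4 shows that ANCOVA would still be at least as precise in large samples.
- The background notes that ROTEM can miss moderate fibrinolysis. If many values show no lysis, the correlation may be low and a linear model may fit poorly.
- The fibrinolysis objective listed under the primary objective names no comparator. The comparison between arms belongs to a secondary outcome, so the trial's primary analysis is not weakened.

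It can also be said that covariates for laboratory outcomes are usually left to a statistical analysis plan, which is not at hand. That would answer a complaint about missing detail. Here, however, the protocol names this outcome and fixes its test, so the choice can be assessed as written.

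**Conclusion.** The point holds as a recommendation to gain precision. For continuous ROTEM measures at all sites, and for Maasstad assays with paired samples, the protocol fixes a valid between-arm test that makes no stated use of a baseline already being collected.

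If unadjusted power were 80%, the gain would be about 2 to 17 points for r between 0.2 and 0.7, and close to nothing for r near zero. Both the 80% and the range of r are assumptions. A reader might infer a definite loss of about 10 points; that figure needs r of about 0.5 together with 80% starting power. The document gives neither for fibrinolysis, and its only 80% belongs to blood loss.

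The primary blood-loss analysis is unaffected. So is the binary occurrence of fibrinolysis, which falls under the chi-squared test.

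**What to change.** In {20a}, replace the two-sample test for continuous ROTEM measures, and for Maasstad assays with paired samples, by this rule. Compare the arms by ANCOVA of the intra-operative value, with arm and the same assay's pre-surgery (pre-infusion) value as terms. Use the log scale if values are skewed, and a rank-based version if many values show no lysis. Report the adjusted difference or ratio with a 95% confidence interval.

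The cost is one degree of freedom and a sentence of text. ROTEM needs no new samples, and the Maasstad assays enter only where pairs already exist. Because {20c} plans no handling of missing data, the sentence should also say how a patient without a pre-surgery value is treated.

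The article expects inclusion to finish in December 2025 and places unblinding after data analysis, so the change can be specified while the allocation is still concealed.

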## Introduction

### Background and rationale {6a}

Major burn trauma involves a complex interplay between activation of coagulation and activation of the immune system [1]. Although the underlying pathophysiology behind these processes is not completely understood, more knowledge became available in recent years. Following severe burn injury, the patient’s coagulation status may change considerably as a response to the systemic inflammatory response and as a result of interventions such as hemodilution and during fluid resuscitation and excisional surgery [2]. The development of coagulopathy has been identified as a risk factor for increased morbidity and mortality after major burn trauma [3, 4]. Despite an increase in knowledge, blood loss during burn excisional surgery remains a major challenge and is an independent predictor of mortality [5]. During burn excisional surgery, limited interventions are available to control the bleeding during surgery. For example, the use of topical adrenalin and topical tranexamic acid and the use of a tourniquet have been described in literature [6]. Despite these techniques, blood loss is still substantial [7].

Cell salvage is a well-known method to reduce allogenic blood transfusion during high blood loss surgery. The use of cell salvage is feasible in burn patients and up to 25% of blood loss can be recovered. However, despite strict sterile handling of shed blood, the erythrocyte concentrate showed substantial bacterial contamination [8].

Reducing blood loss and tailoring blood product administration may improve patient outcome and reduce morbidity and mortality associated with transfusion and blood loss [3]. Therefore, well-functioning coagulation is of the upmost importance.

Normally, coagulation is a balanced process in which there is simultaneous coagulation and fibrinolysis. However, several studies describe a disruption of the immune system and coagulation comparable to changes after major trauma [3, 9, 10]. Marked increase of activation in coagulation paradoxically coexisted with an increase of fibrinolysis [4, 9, 11].

The increased fibrinolysis could be one of the contributing factors of blood loss during burn excisional surgery as fibrinolysis is seen in burn patients [9]. Furthermore, moderate to severe disturbance of the fibrinolytic system is seen in > 50% of all trauma patients [12].

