### Methods in analysis to handle protocol non-adherence and any statistical methods to handle missing data {20c}

The data will be analyzed using an intention-to-treat method without methods to handle missing data.

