### Adverse event reporting and harms {22}

Adverse event (AE), serious adverse events (SAE), and suspected unexpected serious adverse reactions (SUSAR) are monitored and recorded after a patient provides informed consent. Adverse events reported spontaneously by the subject or observed during a routine consultation examination by the investigator, or his staff will be recorded. Adverse events regularly associated with surgery or burn treatment will not be monitored: nausea/vomiting, pain, skin rash of surgery site, diarrhea, edema, hypo-/hypertension, psychosis, delirium. In conformation with the Medical Research Involving Human Subjects ACT, SAE will be reported to the Medical Research Ethics Committee (MREC) within 7 days after first knowledge for SAEs leading to death or that are life threatening and for other SAEs within 15 days of first knowledge. SUSARs will be reported twice yearly as a line list to the MREC. Three months after the intervention, the electronic health record and the participant will be consulted to evaluate possible cardiopulmonary of neurologic complications.

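### Length of hospital and ICU stay is tested with no allowance for in-hospital death, so an early death counts as a short stay (minor; secondary outcome only)

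*Protocol article*

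**What the plan says.** Outcomes {12} lists hospital mortality and length of (ICU) stay as two separate secondary outcomes. I read the second as both hospital and ICU stay.

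Statistical methods for primary and secondary outcomes {20a} gives one rule for continuous secondary outcomes: "For secondary outcome parameters, continuous variables (i.e., volume of blood loss, extent of hyperfibrinolysis) will be tested for normal distribution". It continues: "If they are normally distributed, the mean with standard deviation will be reported and differences will be tested using Student’s" t-test; otherwise a Mann-Whitney test is used. Binary outcomes, and so mortality, have their own rule: "Binomial data will be reported using percentages, and differences will be tested using chi-squared tests".

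The section on non-adherence and missing data {20c} adds: "The data will be analyzed using an intention-to-treat method without methods to handle missing data".

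The article contains no survivors-only, worst-rank, time-to-event or competing-risk rule for stay.

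**The concern.** Stay is cut short by two opposite events, discharge alive and death. A test on the recorded number of days treats them alike. A patient who dies on day 3 contributes a 3-day stay, which ranks among the best values in the trial. Intention to treat keeps that patient in the comparison.

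Death is relevant to this trial. It is a listed outcome, and Background and rationale {6a} says that "blood loss during burn excisional surgery remains a major challenge and is an independent predictor of mortality". The treatment aims at blood loss, so an effect on early mortality in either direction is conceivable. Excess early deaths on tranexamic acid would then pull its stay down, and an early survival gain would push its stay up. At stake is the reading of one secondary outcome.

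**Working it through.** **1. Group size.** The only related figure in the plan is the sample size for the primary outcome, "based on a mean blood loss of 194 ml/% BSA excised with an SD of 81 ml". The target there is a quarter less blood loss, with alpha 0.05 and 80% power. The difference is 0.25 × 194 = 48.5, and 48.5 / 81 = 0.599 SD. A two-sided t-test at 5% with 80% power needs 44.8, so 45 per arm and 90 in total; 90 / 0.95 = 94.7, so 95. The plan's figures reproduce (the article does not state sidedness; two-sided is what reproduces them). I use 45 per arm below.

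**2. Assumptions, none of them from the documents.** Survivors' stay is log-normal with mean 25 days and coefficient of variation 0.8, identical in both arms. Log-variance = ln(1 + 0.8²) = 0.495, so the log-SD is 0.703 and the median is 25 × exp(−0.495 / 2) = 19.5 days. Deaths are uniform over a stated window of days. Mortality rates are varied.

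**3. Direction and size of the shift in means.** With equal stay in survivors,

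difference in mean recorded stay = (p₁ − p₀) × (mean day of death − mean stay of survivors),

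where p₁ is mortality in the arm with more deaths.

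- Deaths on days 2-10 (mean 6): 3% v 6% gives 0.03 × (6 − 25) = −0.6 days; 3% v 10% gives −1.3; 5% v 15% gives −1.9.
- Deaths on days 5-40 (mean 22.5), 5% v 15%: 0.10 × (22.5 − 25) = −0.25 days.
- Deaths on days 20-60 (mean 40), 5% v 15%: 0.10 × (40 − 25) = +1.5 days.

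The sign depends on whether deaths fall before or after usual discharge.

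**4. False favourable results.** This is the simulated share of trials in which a two-sided 5% Mann-Whitney test significantly favours the arm with more deaths (nominal 2.5%).

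| Mortality | Days of death | Recorded stay | Deaths ranked worst |
|---|---|---|---|
| 5% v 5% | 2-10 | about 2.5% | about 2.5% |
| 3% v 6% | 2-10 | about 4% | about 1.4% |
| 3% v 10% | 2-10 | about 7% | 0.6% |
| 5% v 15% | 2-10 | about 10% | 0.3% |
| 5% v 15% | 5-40 | about 2.4% | 0.3% |
| 5% v 15% | 20-60 | 0.7% | 0.3% |

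In the last row, the test on recorded stay points significantly towards harm in about 7.5% of trials, so the bias has reversed. A different survivor distribution (median 21 days, log-SD 0.7, deaths on days 1-14) gives 3.8%, 6.8% and 9.1% for the three unequal contrasts in the order of the table.

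**The case against.** **The article is silent rather than wrong.** Section {20a} does not name length of stay, and its examples are blood loss and hyperfibrinolysis. How a death is scored is often settled in an analysis plan, and one may exist. What stands is that a reader should not infer that the protocol expressly ranks deaths as early discharges; that follows only from applying the general rule. But stay is a continuous secondary outcome, no other stated rule reaches it, and the stated rule includes a t-test on recorded values, so the article fixes a method that suits stay poorly.

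**The effect depends on early deaths.** A reader might infer that stay moves in the wrong direction whenever mortality differs. It does not: with deaths on days 5-40 the excess is gone, and with later deaths the direction turns. The documents say nothing on when deaths occur, or on whether stay runs from admission or from operation. This objection stands in full.

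**The mortality contrasts are large.** 3% v 10% and 5% v 15% are at least threefold increases, while the sections on interim analyses {21b} and data monitoring {21a} describe the risk to patients as low or limited. No mortality rate is given. At 3% v 6% the excess is small.

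**Harm is not hidden.** A reader might infer that a harmful treatment would pass as beneficial. The documents do not support that: mortality is its own outcome with its own test, and fatal serious adverse events go to the ethics committee within 7 days {22}. The distortion is confined to stay.

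**Conclusion.** The point holds in limited form. As written, the analysis of hospital and ICU stay makes no allowance for in-hospital death and is biased in favour of the arm with more early deaths, if early mortality differs. Under the assumptions above, the false favourable rate is about 4% to 10% instead of 2.5% when deaths fall on days 2-10. There is no excess when mortality is equal or deaths are spread over days 5-40, and the bias reverses when deaths are later still. Those sizes illustrate the mechanism and do not predict this trial. The primary outcome, the sample size and the mortality comparison are unaffected. Severity: minor.

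**What to change.** Add one sentence to section {20a}: length of hospital stay and length of ICU stay will be compared by the Mann-Whitney test with in-hospital deaths ranked worse than any survivor, and stay in survivors will be shown descriptively only. This takes stay out of the normality-then-t-test route and uses a test the section already names. It needs only discharge and death dates and does not change the sample size. It should be settled before unblinding, which section {17a} places after data analysis.

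The downside is small: the result becomes a composite of stay and death, so it must be read beside the separate mortality outcome and not as further evidence on mortality.

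Replacing stay by days alive and out of hospital to 3 months would also deal with death, but it is a larger change. The plan says "Three months after the intervention, the electronic health record and the participant will be consulted", but for cardiopulmonary and neurologic complications; readmissions and transfers, which that measure would need, are not mentioned.
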